## Abstract

**Background:**

Drowning is the third leading cause of death for children aged 0–4 years in many Asian countries, and is a serious but neglected health problem in low and middle-income countries like Bangladesh. The aim of the study is to outline the study protocol of a trial to test the efficacy of a mobile coach based intervention for the prevention of childhood drowning.

**Method/design:**

A two-arm cluster randomized community trial will be conducted to test the efficacy of the mobile coach intervention for childhood drowning on parents with children below five years of age and compared to an assessment only control group. A total of 1680 parents in the villages with children aged below five years of age will participate. The village will be used as a randomized unit, randomly assigned to an intervention group (*N* = 840) receiving the mobile coach based intervention or an assessment only control group (*N* = 840). An individualized mobile coach intervention based on the demographic data and the individual will be developed, and SMSs, audio messages, videos and images about childhood drowning will be sent to the participants of the intervention group over a period of six months. The participants will receive per week one text message (SMS) and image and one video and audio text per month. The primary outcome measure will be increased knowledge and safety awareness, and behaviour practice about childhood drowning assessed at the six-month follow-up, and the secondary outcome measure will be the reduced incidence of childhood drowning in Bangladesh. The study assistants conducting the baseline and the follow-up assessments will be blinded regarding the group assignment.

**Discussion:**

This is the first study testing a fully mobile coach intervention for childhood drowning prevention in Bangladesh. It is hoped that the programme will offer an effective and inexpensive way to prevent childhood drowning among children aged below five years and also increase the awareness of parents concerning the risks to their children from drowning.

**Trial registration:**

ISRCTN13774693, 08/03/2015.

## Background

Drowning is the process of experiencing respiratory impairment from submersion or immersion in liquid; outcomes are classified as death, morbidity and no morbidity [1]. Drowning is the third leading cause of unintentional injury worldwide, and constitutes 7 % of all injury related deaths globally. There are an estimated 388,800 annual drowning deaths worldwide. Among children, drowning accounts for a higher mortality rate than any other, and, unfortunately, the drowning rate in Asia is 20 times higher than in developed countries. The parent’s socio-economic status and lack of education, infants left unsupervised, access to water, and children under 5 years of age, especially males, are the factors that represent the greatest risk from drowning [2]. Drowning is the single leading cause of death after infancy, 50 % of drowning occurs between the ages of 0 to 4 years, 60 % happens between 9 a.m. and 1 p.m., 80 % occurs in ponds, ditches, buckets and drums, 80 % happens within 20 m of the child’s home, and children from large families are twice as vulnerable to drowning than those from small families. In Bangladesh, a child drowns every half hour, with a total of 50 per day and 18,225 during the course of a year [3].

Bangladesh is a largely rural low-income country with most households located near bodies of water. Many children do not know how to swim and families are large, leading to decreased adult supervision. These factors combine to make drowning the leading cause of child death after infancy. The drowning mortality rate is 28.6 deaths per 100,000 child-years in Bangladesh, which is 22 times greater than in the Americas [4–9]. The drowning of rural children aged 1–4 years in Bangladesh was found to be 156.4 per 100,000 (95 % CI 138.5 - 176.6 per 100,000) with boys numbering 175.5 and girls 135.8. The proportional mortality from children drowning in respect of the overall child mortality was about 28 %. Ponds, ditches, buckets and drums were the most frequent places of drowning, and over 40 % occurred in ponds. The risk factors include the sex of the identified child, mother’s age and literacy, family income and ownership of agricultural land by the families [10]. The incidence of drowning among children aged 1 – 4 years old was 157 per 100,000 children-years. The highest rate was 328.1 per 100,000 (95 % CI 254.8 – 421.7) among 1 year old male children. The risk factors include mothers’ age, literacy and family income. Male children from poor families were at great risk of drowning in rural Bangladesh [11–13].

### What are the risks?

Drowning happens in many different ways, and needs a range of prevention strategies to target the biggest risks. The main risk factors are: Lack of physical barriers between people and water, particularly close to home, Lack of supervision of young children, Uncovered or unprotected water supplies and lack of safe water crossings, Lack of water safety awareness and risky behaviour around water, such as swimming alone, Travelling on water, especially on overcrowded or poorly maintained vessels, Flood disasters, whether from extreme rainfall, storm surges, tsunamis or cyclones [14].

### Governmental goals in Bangladesh

Today, injury is the biggest killer of Bangladeshi children between 1–18 years, and the greatest danger is from drowning. The remarkable progress made in the reduction of child mortality from infectious diseases in Bangladesh during the last two decades has meant that injuries are now emerging as a greater threat to child survival. Although the rate of drowning has remained stable since the 1980s, drowning as a proportion of all deaths in children aged 1–4 increased from 9 % in 1983 to 59 % in 2003. Bangladesh Target: To reduce deaths of children under five by two-thirds by 2015; that is, reduce the under-five mortality rate to 48 deaths per 1000 live births [15].

### How can the threat of drowning be reduced?

Drowning can be prevented through targeted prevention strategies, improved community infrastructure (water supply, bridges, levees, etc.), public awareness, appropriate policies and legislation, and research that refines what is seen as best practice and that identifies new drowning prevention measures. Such measures include: Reduced exposure to water hazards through the strategic use of barriers, Comprehensive boating regulations and enforcement, Close and capable adult supervision for young children, Signage and designation of hazardous water bodies, Improved swimming and water safety skills, Timely rescues and resuscitation by a trained bystander or lifesaver through mouth-to-mouth resuscitation and chest compression when needed, Requirements for use of personal flotation devices and Supervision of recreational swimming areas [14].

Therefore, the aim of this study is a trial to test the efficacy of a *MOBILE COACH* based intervention for the prevention of childhood drowning in Bangladesh.

### Research objectives

#### Main objective

❖ To develop and implement effective mobile coach intervention on childhood drowning prevention among parents with children’s age below five years in rural areas in Bangladesh

#### Specific objectives

❖ To determine the differential between the ages and gender of the children in respect of knowledge, awareness, practice and child drowning.❖ To develop and assess the initial response of a community to an intervention package in terms of acceptability, feasibility and sustainability.❖ To determine the social-demographic factors (educational level of parents, occupation of parents, social-economic status of parents and medical condition), environmental factors (places of residence, time of day, time of season, distance from the house, place of drowning, safety equipment, presence of lifeguard, activity immediately before drowning and mothers activity) and behavioural factors (supervision practices of parents and swimming ability of parents and child) through pre-test and post-test on knowledge, awareness, practice and child drowning.❖ To understand the perception of the community concerning the problem of drowning and its possible implications for designing a preventive programme for the rural areas of Bangladesh.❖ To identify the association between the knowledge, awareness and practice of child drowning with social-demographic variables, environmental variables and behavioural factors.❖ To evaluate the mobile coach for its effectiveness.❖ To determine the risk factors based on social-demographic, environmental and behavioural factors in respect of childhood drowning, knowledge, awareness and practice pertaining to child drowning.

## Method/design

### Design and main hypothesis

A two-arm cluster randomised community trial will be conducted to test the efficacy of the mobile coach based intervention for the prevention of childhood drowning among parents with children aged below five years compared to an assessment only control group. In respect of the childhood drowning knowledge, awareness and practice, SMSs, videos, audio messages and images will be sent to participants based on the Ministry of Health and Family Welfare, Bangladesh Government and Centre for Injury Prevention and Research, Bangladesh. The mobile coach will be sent to the participants over a period of six months and data will be gathered at baseline, with a weekly SMS and images, and monthly videos and audio assessment. The main hypothesis is that the integrated intervention will be a more effective and inexpensive way to prevent childhood drowning among children aged below five years, and also increases the parent’s awareness of their children in respect of drowning. At the six-month follow-up, the primary outcome will be the per monthly increase in knowledge, safety awareness and behavioural practice in respect of childhood drowning prevention of the intervention group compared to those in the assessment only control group. The secondary outcome measures will be reducing the incidence of childhood drowning to compare the baseline and end line assessment with the self-efficacy for childhood drowning prevention, and also to determine the risk factors for childhood drowning. An overview of the study design is presented in Fig. 1.

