#### End line survey

The end line survey for the intervention areas will be conducted in the last surveillance round. About 1680 households will be covered by 15 study assistants. Two supervisors will supervise the activities of the study assistants. The end line survey will use the same instruments as those used in the baseline survey and the same procedure will be followed to collect data. The survey will be conducted over 15 days.

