### Data analyses

The data will be entered into SPSS statistical package version 22.0.

The proportion, mean and standard deviation will be used to quantify the level of knowledge, awareness and practice before and after intervention.

The paired *t*-test will be used to examine the effectiveness of the intervention programme by comparing the pre-test and post-test score in respect of knowledge, awareness and practice.

The chi-square test will be worked out to determine the association of the socio-demographic, environmental and behavioural factors with childhood drowning.

In addition, the risk factors for childhood drowning with socio-demographic, environmental and behavioural factors will be determined using multivariate logistic analysis.

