### Outcomes

The outcomes of the study will be to determine the knowledge, awareness and behaviour practices about childhood drowning, as well as the risk factors, and reduce the incidence of childhood drowning. To determine the knowledge pertaining to childhood drowning, five questions about the knowledge of childhood drowning are provided. The questions will be answered YES or NO. A correct answer will score one mark and a zero mark will be given for an incorrect answer. The participants will be classified as having knowledge of drowning if they correctly answer all five questions. Based on those five questions, the total summated score will be calculated. Five questions will be used to measure the awareness about childhood drowning. Based on the five questions, the total summated score will be calculated. The behaviour practices will be divided into supervision practices and swimming ability. In addition, five questions will be used to measure the behaviour practices. Based on the five questions, the total score will be calculated. The study assistants will conduct the six-month follow up assessment by field interviews. The primary outcome will be the monthly assessment of increased knowledge, and safety awareness and practice about childhood drowning. The secondary outcome will be the assessment of reducing the incidence of children drowning to compare the baseline data and end line data, and also to determine the risk factors for childhood drowning. Finally, the outcome variables will be the effects of the mobile coach Intervention on the community in Bangladesh.

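### The primary effect is worded as an increase and the only stated effectiveness test subtracts baseline; adjusting for the baseline score already collected would usually be more precise at almost no cost.

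*Protocol article*

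**What the plan says.** Design and main hypothesis states that "the primary outcome will be the per monthly increase in knowledge, safety awareness and behavioural practice in respect of childhood drowning prevention". The contrast it sets, at six months, is between arms: the increase is that "of the intervention group compared to those in the assessment only control group". Outcomes words it again as an increase: "The primary outcome will be the monthly assessment of increased knowledge, and safety awareness and practice about childhood drowning".

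Outcomes builds knowledge, awareness and practice from five questions each. For knowledge, "A correct answer will score one mark and a zero mark will be given for an incorrect answer", and "Based on those five questions, the total summated score will be calculated", so that score runs from 0 to 5. A yes/no version stands beside it: "The participants will be classified as having knowledge of drowning if they correctly answer all five questions". The marks per question are not given for awareness or practice.

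The baseline value is available, because "The end line survey will use the same instruments as those used in the baseline survey". Under Data analyses, effectiveness is examined by a paired t-test "comparing the pre-test and post-test score in respect of knowledge, awareness and practice". The only multivariable model in that section is a logistic analysis of risk factors for drowning, not of these scores.

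**The concern.** A paired t-test works on end line minus baseline, which fixes the baseline coefficient at 1 and leaves no place for a covariate. If that form is carried into the comparison of arms, the baseline's measurement error is added to the outcome. On a short bounded score such as knowledge, the increase also depends on the starting point: a parent at 5 cannot rise and a parent at 0 cannot fall. With few villages per arm, chance baseline differences between arms are plausible, and a raw increase carries them into the estimate through regression to the mean.

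What is at stake is precision. The information that would recover it is already collected, and the article gives no reason for preferring the raw increase.

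**Working it through.** **The plan's own power figure.** From Sample size calculation: P1 = 0.55, P2 = 0.45, two-sided 5%, power 80%.

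- N = (1.960 × √(2 × 0.5 × 0.5) + 0.842 × √(0.55 × 0.45 + 0.45 × 0.55))² / 0.10² ≈ 392 per group.
- 392 × 1.10 = 431.
- Design effect as calculated there: 1 + (20 − 1) × 0.05 = 1.95. 431 × 1.95 = 840 per group.

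The arithmetic reproduces as printed. However, the 80% is for the proportions of drowning in boys and girls, not for any score. Below, 80% serves only as a reference point.

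**Raw increase against baseline adjustment.** Assume equal score variance σ² at both times and correlation rho, the same within and between villages. The article gives neither figure.

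- Variance of the raw increase: 2σ²(1 − rho).
- Variance after adjustment for baseline: σ²(1 − rho²).
- Ratio, adjusted to raw: (1 + rho)/2.
- Power after adjustment, from 80% on the raw increase: Φ[(1.960 + 0.842)/√ratio − 1.960].

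| rho | ratio | power, raw increase | power, adjusted |
|---|---|---|---|
| 0.3 | 0.65 | 80% | 93.5% |
| 0.5 | 0.75 | 80% | 89.9% |
| 0.7 | 0.85 | 80% | 86.0% |
| 0.8 | 0.90 | 80% | 84.0% |

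Taken the other way at rho 0.5, if the adjusted analysis had 80% power, the raw increase would have 67.9%. Below rho 0.5, 2(1 − rho) exceeds 1, so subtracting baseline is worse than ignoring it.

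**Does this survive clustering?** Take the article's intra-cluster correlation of 0.05 and assume a within-village rho of 0.5. Let r be the correlation of the village components over time. Consider 28 villages per arm (840/30), 15 (Baseline survey; 840/15 = 56 parents each) and 5 (Study settings and population; 840/5 = 168 each). With m parents per village and σ² = 1:

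- Variance of a village mean: V = 0.05 + 0.95/m.
- Covariance of its baseline and end line means: C = 0.05r + 0.95 × 0.5/m.
- Raw increase: 2(V − C).
- One parent-level covariate with coefficient 0.5: V + 0.25V − C.
- Village mean baseline entered separately: V − C²/V.

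At r = 0.5 every ratio to the raw increase is 0.75, whatever the number of villages. Otherwise:

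| villages per arm | r | ratio, parent covariate only | ratio, with village mean | power, with village mean |
|---|---|---|---|---|
| 28 | 0.7 | 0.83 | 0.81 | 87.5% |
| 15 | 0.7 | 0.86 | 0.83 | 87.0% |
| 5 | 0.7 | 0.89 | 0.84 | 86.4% |
| 28 | 0.9 | 0.99 | 0.87 | 85.1% |
| 15 | 0.9 | 1.12 | 0.90 | 84.0% |
| 5 | 0.9 | 1.39 | 0.93 | 82.8% |

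Worked example, 5 villages, r = 0.9: V = 0.05565 and C = 0.04783. Raw increase 0.01565, parent covariate only 0.02174 (ratio 1.39), village mean included 0.01455 (ratio 0.93). These are large-sample variances and ignore the cost of estimating the coefficients.

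**The case against.** The strongest reply is that the article names no between-arm estimator. A reader might infer that it fixes an unadjusted comparison of raw increases. It does not: the paired t-test contains no arm term, and no other test of the scores is given. Nor does an outcome worded as an increase exclude a baseline covariate. Regressing the increase on arm and baseline gives the same arm effect and standard error as regressing the end line score on arm and baseline. Covariates are also commonly left to an analysis plan. This stands, and it makes the loss conditional on how the arms are compared. It does not remove the point, because the one effectiveness test that is named subtracts baseline and cannot take a covariate.

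That the paired test compares no arms is a separate and larger problem. Repairing it by comparing mean increases, the most literal reading of the outcome, would leave this loss in place.

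Three further limits stand:

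- A 0 to 5 range is explicit only for knowledge, and a yes/no classification competes with it.
- The outcome is called monthly. Dividing a six-month increase by six would change nothing above, but if repeated monthly scores were analysed, the two-time formulas would not apply.
- It is tempting to say that the raw increase is never the more precise choice. With a single parent-level covariate that is false, as the ratios of 1.12 and 1.39 show.

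**Conclusion.** The point holds as a conditional loss of precision. The outcome wording and the only named effectiveness test both work with the difference from baseline, and no stated effectiveness analysis uses the baseline score as a covariate. If the arms are compared on the raw increase, the illustrative cost relative to adjustment is about 4 to 13.5 points of power for rho from 0.8 down to 0.3, and about 10 points at 0.5. This rests on equal variances, one correlation at both levels, two measurement times and 80% as the starting power.

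A reader might take the 10 points as a shortfall of this trial's stated power. The article does not support that, since its 80% concerns drowning proportions. Nor should the point be read as bias: under randomisation an unadjusted comparison of increases is unbiased in expectation, even though a chance baseline imbalance can move a single estimate. If village components correlate at 0.7 to 0.9 over time while the within-village rho is 0.5, the gain with the village mean included is about 3 to 7.5 points.

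**What to change.** In Design and main hypothesis and in Data analyses, state that each six-month score is compared between arms in a model that accounts for village, adjusted for the same parent's baseline value of that score and for the village mean baseline score. Entering the village mean separately guards against the reversal shown above. Report the mean increase per arm as a descriptive summary.

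The cost is a change of wording and one or two covariates, with no new data, visits or participants. With only 5 villages per arm, the village mean uses one of few village-level degrees of freedom (10 − 2 = 8 becomes 10 − 3 = 7, so the two-sided 5% t value rises from 2.31 to 2.36). With 15 or more villages per arm the cost is negligible.

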#### Study duration

The duration of the study is six months. The activities of the intervention programme will commence in March 2015 and end in August 2015.

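### Drowning incidence is too rare in this trial to show a reduction or its risk factors, and the stated before-after comparison does not use the randomised control

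*Protocol article*

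**What the plan says.** The comparison for drowning incidence is stated twice. Under Design and main hypothesis: "The secondary outcome measures will be reducing the incidence of childhood drowning to compare the baseline and end line assessment". Under Outcomes, the secondary outcome is "reducing the incidence of children drowning to compare the baseline data and end line data". In the first of these sections the comparison with the control group is attached to the primary outcome (knowledge, awareness and practice), while the main hypothesis itself names prevention of childhood drowning.

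Data analyses gives a chi-square test for the association of factors with drowning and adds that "the risk factors for childhood drowning with socio-demographic, environmental and behavioural factors will be determined using multivariate logistic analysis". It names no between-arm test of incidence.

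The Background supplies the rates: "The drowning of rural children aged 1–4 years in Bangladesh was found to be 156.4 per 100,000", with a 95% interval of 138.5 to 176.6, and "The incidence of drowning among children aged 1 – 4 years old was 157 per 100,000 children-years". A lower figure also appears: "The drowning mortality rate is 28.6 deaths per 100,000 child-years in Bangladesh". On timing, "The activities of the intervention programme will commence in March 2015 and end in August 2015", and the baseline survey takes place one month before implementation. The End line survey section gives about 1680 households.

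**The concern.** A reduction in drowning is part of the main hypothesis, an aim of the intervention and a secondary outcome. The article gives a rate, a number of households and a follow-up time, but never multiplies them into an expected number of events. If that number is one or two, the comparison cannot inform in either direction: no difference would not show lack of effect, and a difference would rest on one or two children.

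The stated contrast adds a second problem. Comparing baseline with end line gives up the protection that randomising villages provides. The two assessments may differ in look-back period, in season and in how cases are found (one survey against monthly household visits). The article itself lists floods as a risk and season as a factor of interest.

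The third problem is the risk-factor model. It needs many more events than follow-up can supply, whatever factors are chosen.

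**Working it through.** **The plan's own figure.** No expected number of drownings is stated. The sample size is, and it reproduces. With proportions 0.55 and 0.45, two-sided 5% and 80% power, n = (1.96 × √0.5 + 0.8416 × √0.495)² / 0.10² ≈ 392. Then 392 × 1.10 = 431, and 431 × 1.95 = 840 per group, 1680 in total. The two proportions are the shares of drownings in boys and girls, so this calculation gives no support to a comparison of incidence.

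**Inputs.** Rate 156.4 per 100,000 (Background; the companion figure of 157 gives the unit as child-years). Households 1680, or 840 per arm (Sample size calculation, End line survey). Follow-up 0.5 year (Study duration). Children under five per household: not stated. I assume 1 and show up to 4, because eligible parents have fewer than five children.

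**Expected drownings, no effect assumed** = households × children per household × 0.5 × rate.

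One child: 1680 × 0.5 × 0.001564 = 1.31 in total, 0.66 per arm. The chance of none in a given arm is exp(−0.657) = 52%, and of none in the trial exp(−1.314) = 27%.

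| Children under five per household | Expected total | Expected per arm | Power for a halving |
|---|---|---|---|
| 1 | 1.31 | 0.66 | 0.005% |
| 1.5 | 1.97 | 0.99 | 0.03% |
| 2 | 2.63 | 1.31 | 0.13% |
| 4 (extreme) | 5.26 | 2.63 | 1.6% |

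Power is for an exact conditional two-sided test of two Poisson counts with equal child-years, ignoring clustering. The reason it is so low: with five events all in one arm p = 2 × 0.5⁵ = 0.063, so at least six events, all in one arm, are needed (2 × 0.5⁶ = 0.031). Even complete elimination of drowning at four children per household gives only about 5%.

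**Other rates, one child per household.** Over the cited interval the total is 1.16 to 1.48. At 28.6 per 100,000 it is 0.24. If every child had the highest subgroup rate cited (328.1 per 100,000, one-year-old boys) it is 2.76.

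**Ten times the rate** (assumption, to allow for non-fatal events). Expected counts of 6.6 against 3.3 per arm give about 10% power with one child per household, and 9.9 against 4.9 give about 17% with 1.5. With two children it is about 24%, and at the extreme of four about 50%. All ignore clustering, which would lower them.

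**What a halving would need at 80% power.** Child-years per arm = (1.96 + 0.8416)² × (r + r/2) / (r/2)² with r = 0.001564, which is about 30,100. That is about 60,200 children per arm followed for six months, or about 117,000 with the protocol's design effect of 1.95.

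**Surveillance coverage.** Injury surveillance describes six blocks of 100 to 150 households, or 600 to 900. If that is the whole surveillance population, the expected total at one child per household is 0.47 to 0.70.

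**Risk-factor model.** Specific objectives lists about 15 socio-demographic, environmental and behavioural factors. Against roughly 1 to 5 follow-up events, no multivariable model with several groups of factors can be supported. Two of the listed items, where the drowning happened and what the child was doing just before, have no value for a child who did not drown. They cannot be predictors at any sample size.

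**The case against.** Several stronger readings are tempting, and the document does not support them.

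- *That the result will be a seasonal artefact.* Only the baseline interview is dated. Its look-back is not given, and a 12-month recall would span all seasons. Confounding by season is possible, not shown.
- *That the trial will certainly see about one event.* Children per household is not stated, and the Background defines drowning outcomes to include morbidity and no morbidity. If non-fatal events count, there will be more. The article gives no non-fatal rate and does not say that they count.
- *That the logistic model cannot be fitted at all.* Data analyses does not restrict drowning to follow-up or to deaths, so events reported at baseline might be included. Nor does it say that all of the roughly 15 factors enter one model.
- *That a between-arm comparison is ruled out.* The trial is described as controlled, the baseline survey covers both arms and the end line count of 1680 matches both. A comparison of change between arms could be set out in an analysis plan.

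Incidence is also only a secondary outcome, and this point leaves the primary outcome untouched.

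These arguments limit how firmly the consequences can be put. They do not rescue the comparison: no analysis plan can draw an effect from one to five events, the baseline-to-end-line contrast is written twice, and the main hypothesis names prevention of drowning.

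**Conclusion.** The point holds for the size of the incidence comparison, for its stated form and for the use of follow-up drownings to identify risk factors. At the protocol's own rate the trial expects about 1.3 drownings (5.3 at the extreme of four children under five per household), and power to detect a halving is below 2% throughout. A tenfold rate gives about 10 to 17% at one to 1.5 children per household and stays well short of 80% even at four. These figures apply the rate for ages 1 to 4 to every child under five, assume full six-month follow-up and ignore clustering.

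The before-after contrast would not be a randomised comparison, and its periods and ascertainment may differ. Risk-factor conclusions from so few follow-up events would be unsupported. As planned, an apparent reduction could not be attributed to the intervention, and finding none would say nothing about it.

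**What to change.** - In Design and main hypothesis and in Outcomes, make drowning a descriptive outcome: events and child-years by randomised arm over the same March to August period, with exact Poisson intervals, no baseline-to-end-line test and no claim of reduced incidence. Word the main hypothesis to match.
- In Data analyses, drop the multivariable drowning model, or reduce it and the chi-square tests to a description of the cases. Items that exist only for children who drowned belong in that description. Apply the factor analysis to the knowledge, awareness and practice scores, allowing for clustering by village; this also serves the association objective already listed.
- State whether non-fatal events count.
- Confirm that surveillance covers all participants in both arms, since 600 to 900 households is fewer than 1680. If it does not, take events from the end line survey of both arms. That section speaks of intervention areas while its 1680 households match both arms, so its coverage should be made explicit too.

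The cost is a more modest claim and an amendment to the wording of the secondary outcome and the hypothesis in a registered, ethics-approved trial. Extra data collection is needed only if neither surveillance nor the end line survey covers both arms.
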